## Abstract

**Background:**

Coronary heart disease (CHD) is a major cause of morbidity and mortality in Australia and it is recommended that all persons with unstable angina (UA) or myocardial infarction (MI) participate in secondary prevention as offered in cardiac rehabilitation (CR) programs. However, the majority of patients do not access standard CR and have higher baseline coronary risk and poorer knowledge of CHD than those persons due to commence CR. The objective of this study is to investigate whether a modular guided self-choice approach to secondary prevention improves coronary risk profile and knowledge in patients who do not access standard CR.

**Methods/Design:**

This randomised controlled trial with one year follow-up will be conducted at a tertiary referral hospital. Participants eligible for but not accessing standard CR will be randomly allocated to either a modular or conventional care group. Modular care will involve participation in individualised modules that involve choice, goal-setting and coaching. Conventional care will involve ongoing heart disease management as directed by the participant's doctors. Both modular and conventional groups will be compared with a contemporary reference group of patients attending CR. Outcomes include measured modifiable risk factors, relative heart disease risk and knowledge of risk factors.

**Discussion:**

We present the rationale and design of a randomised controlled trial testing a modular approachfor the secondary prevention of coronary heart disease following acute coronary syndrome.

## Background

Coronary heart disease (CHD) is a major cause of morbidity and mortality in Australia and is associated with significant cost [1]. Australian guidelines recommend all persons with unstable angina (UA) or myocardial infarction (MI) participate in secondary prevention [2] incorporating risk factor management. Risk factor modification including lifestyle change and the use of vasoprotective medications is an effective means extending overall survival, reducing non-fatal cardiovascular events, decreasing the need for coronary revascularisation, enhancing quality of life (QOL) [3] and improving coronary endothelial function [4,5]. Importantly, CHD is a chronic illness that is best managed when positive health behaviors become integrated into long-term lifestyle habits therefore, strategies are needed to motivate and support patients to consistently follow multidimensional treatment regimens.

Cardiac rehabilitation is a widely recognised form of secondary prevention [6], but participation rates are low (10–30%) [7,8] because of transport difficulties, work and social commitments and a lack of perceived need [9]. Despite clear short-term benefits for attendees, large groups of patients are not benefiting, which presents an opportunity and challenge to improve CHD care [10]. Importantly, there are limited studies reporting the risk profile of patients not accessing formal rehabilitation. One observational Australian study demonstrated that non-participants were at higher risk of recurrent events than patients attending rehabilitation [11]. Similarly, functional impairment has been shown to be the strongest predictor of non-participation in cardiac rehabilitation after coronary artery bypass graft surgery [10]. These findings are of major concern because the patients who stand to benefit the most from secondary prevention are the people least likely to participate.

One pilot study has clinically investigated secondary prevention of CHD using a 'modular' approach and demonstrated enhanced completion rates and cost effectiveness [12]. For the study, a metropolitan cardiac rehabilitation program was offered as individual components, or modules, based on patient need rather than an all-or-nothing exercise-based approach. The pilot study was an important step from standard cardiac rehabilitation however, the modules were still conducted in a group environment and were predominantly based on education without formal goal setting and follow-up. Results of the pilot study suggest it is likely that the development and evaluation of more detailed unique risk factor modules may enhance long-term outcomes.

The inclusion of multidimensional behavior modification techniques such as goal setting and offering a wide range of individually tailored services may enhance compliance with long-term risk factor interventions [13]. For chronic disease, it is important to conceptualise change in a positive light to reduce anxiety about the disease rather than focusing on negative aspects of making a change [14]. Setting of mutually-agreed, realistic and readily identifiable goals with clear time frames helps enhance active patient orientation and motivation and therefore facilitates behavior change [14,15]. Further, the inclusion of a rating of confidence for goal achievement may improve the health professional's insight into a patient's intrinsic motivation to change [14].

Facilitation of collaborative relationships, shared decision-making, offering choice and communication of expectations in a supportive environment helps motivate behavior change and therefore contributes to the disease management process [15,16]. Formation of collaborative relationships decreases patient anxiety and dissatisfaction that is often related to uncertainty and lack of information, explanation and feedback [17]. Studies have demonstrated that encouraging patients to participate in treatment decisions improves health status, QOL [18,19], satisfaction, compliance and treatment outcomes [20]. More specifically, patients with a higher degree of active orientation are more likely to comply with treatment recommendations for BP [16], diabetes and physical activity [21]. Offering choice, in situations where there are several management options based on individual preferences or circumstances is a further method of enhancing active patient orientation [22]. It is also suggested that options offered as a menu of strategies are more successful because it encourages each patient's task to be one of "choosing rather than refuting" [14]. We have chosen the term 'guided self-choice' to describe this model which creates a collaborative encounter, similar to the spirit of behavior counseling [23].

The objective of this study is to investigate whether a modular guided self-choice approach to secondary prevention improves coronary risk profile and knowledge in acute coronary syndrome (ACS) patients who do not access standard cardiac rehabilitation.

## Methods/Design

### Design

This randomised controlled trial with one year follow-up will be conducted at a tertiary referral hospital in Sydney, Australia. Participants not attending standard cardiac rehabilitation will be randomly allocated to either a modular secondary prevention (experimental) or a conventional care (control) group. A third contemporary group of patients attending standard cardiac rehabilitation will also be recruited (reference group). Ethical approval for the study has been granted by both the Central Sydney Area Health Service CRGH Zone and the University of Sydney Human Research Ethics Committees. Written and informed consent will be obtained from all participants prior to commencement.

Independent variables are the identification of individualised risk factor goals and participation in self chosen secondary prevention modules. The dependent variables are assessment of cardiac risk factors, the achievement of risk factor goals, unplanned hospital readmissions, quality of life, relative cardiac risk and knowledge of risk factors. The measurement and recording of experimental variables will be conducted under blind conditions.

### Study population

To establish a recruitment database, a list of all admissions to a single metropolitan tertiary referral hospital in Sydney Australia, with an ACS during a 10 month period, was obtained using diagnostic related codes [24] for UA (F72A, F72B), MI (F41A, F41B, F60A, F60B) and chest pain (F74Z). For all admitted patients, the hospital medical records were reviewed to determine secondary prevention eligibility. Reasons for ineligibility included geography (living outside a 20 km radius of the hospital), insufficient English language to provide informed consent, congestive heart failure, the presence of a severe co-morbidity (eg, end stage renal disease, Parkinson's disease, cancer) and death.

Inclusion criteria for the randomised conventional care and modular groups were:

- No previous attendance at a formal cardiac rehabilitation program including those who refused the initial invitation to participate and those who failed to attend the initial cardiac rehabilitation assessment.

- Diagnosis of ACS in the six months prior to recruitment.

- Ability to understand sufficient English to give written and informed consent.

Inclusion criteria for non-randomised standard rehabilitation group were:

- Commencing attendance at the CRGH cardiac rehabilitation program during the data collection period of the study.

- Diagnosis of ACS in the six months prior to recruitment.

- Ability to understand sufficient English to give written and informed consent.

Exclusion criteria were the same for all three groups in the study and were:

- Clinical diagnosis of uncompensated, severe cardiac failure (Class IV).

- Uncontrolled arrhythmia or angina

- Severe or symptomatic aortic stenosis

- Persistent hypotension (SBP < 90 mmHg)

- Clinical diagnosis of a severe co-existing medical condition that would prevent participation (eg, dementia, a rapidly deteriorating terminal illness or severe or active rheumatoid arthritis)

Once the database of eligible patients is constructed, all patients will be contacted by mail and telephone and asked to volunteer for research investigating heart disease risk factors. Recruitment mail-outs will be conducted in batches of 30 to enable staggered recruitment over approximately six months. Patients will be contacted within two weeks of the mail-out to establish whether they would be prepared to volunteer.

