### Group allocation

For the standard cardiac rehabilitation group, participants will be consecutively recruited prior to commencement of outpatient cardiac rehabilitation. Patients who are eligible for but not participating in cardiac rehabilitation will be randomly allocated to either their modular or conventional care group immediately following completion of the baseline assessment. Therefore, the researcher conducting each baseline assessment will be blinded to group allocation. Prior to study commencement, a computer-generated allocation sequence will be constructed using randomly permutated blocks [25]. An individual not involved in the study recruitment, data collection or analysis will produce consecutively numbered sealed opaque envelopes containing each participant's allocation. Following baseline assessment, the researcher will select the next consecutively numbered envelope and open it to reveal the allocated group. They will then notate the unique patient identifier on the front on the participants cover sheet. Therefore, group allocation will be concealed from the researcher conducting baseline assessments.

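### Contrasts with the non-randomised rehabilitation group are confounded but get the same tests as the randomised contrast, and the two printed eligibility lists do not agree

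*Protocol article*

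**What the plan says.** **Planned comparison.** The Abstract (Methods/Design) states: "Both modular and conventional groups will be compared with a contemporary reference group of patients attending CR". The Discussion calls the rehabilitation outcomes benchmarks.

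**Recruitment routes.** Study population describes a recruitment database built from hospital admissions and screened by record review: "Once the database of eligible patients is constructed, all patients will be contacted by mail and telephone". The reference group enters differently. Group allocation says: "For the standard cardiac rehabilitation group, participants will be consecutively recruited prior to commencement of outpatient cardiac rehabilitation". Study population labels this group openly: "Inclusion criteria for non-randomised standard rehabilitation group were".

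**Known differences.** The Abstract (Background) says that the majority of patients do not access standard rehabilitation and "have higher baseline coronary risk and poorer knowledge of CHD than those persons due to commence CR". The main Background section adds an observational study in which non-participants had a higher risk of recurrent events.

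**Eligibility.** For the database screen: "Reasons for ineligibility included geography (living outside a 20 km radius of the hospital), insufficient English language to provide informed consent, congestive heart failure", followed by severe co-morbidity and death. Later in the same section: "Exclusion criteria were the same for all three groups in the study". The heart-failure item in that common list begins "Clinical diagnosis of uncompensated, severe cardiac failure (Class IV", and the list contains no distance rule.

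**Analysis.** Data analysis assigns differences between and within groups to repeated measures ANOVA for continuous outcomes and to chi-square or Fisher tests for proportions. Significance is two-sided p < 0.05. It does not distinguish the randomised contrast from those with the reference group.

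**The concern.** Attenders and non-attenders differ in risk and knowledge before any programme acts, and these are the domains the trial measures as outcomes. A p-value for modular versus rehabilitation, or conventional versus rehabilitation, therefore mixes programme effect with self-selection, recruitment route and possibly time since the acute coronary syndrome (ACS). Giving such a p-value the same test and threshold as the randomised contrast invites the same causal reading.

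The chi-square and Fisher tests cannot adjust for anything, so smoking status, activity category and other proportions would be compared raw. For continuous outcomes a group-by-time term takes some account of starting level. It does not deal with differential regression to the mean, time since ACS or other prognostic differences.

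The eligibility mismatch adds a second problem. A reader cannot tell whether the three groups were drawn under the same restrictions on heart failure and distance, and so cannot tell how far the groups are comparable.

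**Working it through.** **1. The plan's own figure.** Sample size uses a 0.5 SD difference, 80% power, two-sided alpha 0.05 and 10% loss.
- Normal approximation: n = 2 × (1.96 + 0.84)² / 0.5² = 62.7, so 63 per group. The t-based solution is 64.
- With loss: 64 / 0.9 = 71.1, so 72 per group.

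The stated 72 reproduces, with 64 evaluable per group.

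**2. Critical difference at one visit.** Inputs: 64 per group (step 1) and SD 0.7 mmol/L for total cholesterol (Sample size).
- Standard error = 0.7 × √(2/64) = 0.1237 mmol/L.
- Critical t on 126 degrees of freedom = 1.979.
- Critical difference = 1.979 × 0.1237 = 0.245 mmol/L.

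**3. False significance when the programmes do not differ.** The documents give no cholesterol gap between attenders and non-attenders, so the gap is an assumption, shown over a range. Here, residual means whatever remains after any handling of baseline. The probability of p < 0.05 comes from the non-central t distribution with non-centrality = gap / 0.1237.

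| Residual gap (mmol/L) | In SD units | Non-centrality | Chance of p < 0.05 |
|---|---|---|---|
| 0 | 0 | 0 | 5% |
| 0.1 | 0.14 | 0.81 | 13% |
| 0.3 | 0.43 | 2.42 | 67% |
| 0.5 | 0.71 | 4.04 | 98% |

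These figures are for a single-visit comparison of two groups. A baseline gap that stays constant over time cancels from a group-by-time test. In that test only a gap that changes between visits produces bias.

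**4. The two eligibility lists side by side (both in Study population).**

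| Item | Database record review | List said to be common to all three groups |
|---|---|---|
| Heart failure | Congestive heart failure, no grade given | Uncompensated, severe, Class IV |
| Distance | Beyond 20 km ineligible | No rule |
| Severe co-morbidity | Ineligible if present | Ineligible if it would prevent participation |

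English sufficient for consent is required of every group. The absence of previous rehabilitation is listed for the randomised groups only, largely because non-attendance defines that population. The section never says whether the record-review screen applied to patients entering rehabilitation.

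**The case against.** The strongest reply is that the main objective concerns patients who do not access rehabilitation. It is answered by modular versus conventional care, which is randomised with concealed allocation. The third group is openly described as non-randomised, a reference and a benchmark, and nothing in the article claims equivalence. This stands, and it limits the point to the secondary contrasts.

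Four stronger readings are tempting but not supported:

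- *The reference group was enrolled under looser eligibility.* Record review is described for all admitted patients, and rehabilitation entrants may have been among them. The different recruitment route makes looser entry plausible, but the text does not say so. Only the disagreement between the two lists is demonstrable.
- *No adjustment will be made.* The article is condensed, and a fuller plan may name covariates. What can be said is that the tests it names do not adjust for confounders, and that it applies them to all between-group differences without distinction.
- *Adding the third group weakens the randomised test.* The article does not specify a single three-group model. Even if it did, the effect depends on where the reference group lies. With a 0.5 SD effect and visit correlation 0.5, omnibus group-by-time power is about 74% with the reference group midway between the arms, against 84% for two arms. With the reference group equal to either arm, it is about 86% to 87%. There is no general loss.
- *A baseline cholesterol gap passes in full into the result.* That is true of a group main effect. It is not true of group-by-time, where a constant gap cancels.

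**Conclusion.** The point holds for the reference-group contrasts. They compare self-selected attenders with non-attenders whom the article itself describes as higher risk and less informed, and they use tests that leave most of that difference in place. The randomised contrast is not confounded.

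The size of the bias cannot be known from the documents. The 13% to 98% range rests on an assumed residual gap of 0.1 to 0.5 mmol/L, SD 0.7 mmol/L, 64 evaluable per group and a single-visit comparison. It shows that gaps well within the 0.5 mmol/L the trial treats as clinically significant could produce a significant result with no programme difference.

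The inconsistency between the two eligibility lists is certain, because both are printed in the same section. Whether it made the groups differ in practice is not established.

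**What to change.** 1. State that the main test uses the two randomised arms only.
2. Reconcile the record-review reasons with the common exclusion list, including the two heart-failure wordings and the distance rule, and state which apply to the reference group. Then either apply the same record-review screen to that group or restrict its comparison to patients who meet it. Which heart-failure criterion is right is for the investigators to settle.
3. Report both reference-group contrasts as observational estimates with 95% confidence intervals. Adjust for the baseline value, age and nature of ACS, which Outcome measures lists as collected. Add sex and time since ACS where the demographic and eligibility records supply them. Neither is listed as an assessment item, although the six-month entry window implies that an ACS date is known.
4. Use regression models for categorical outcomes in these contrasts, in place of chi-square or Fisher tests.
5. State that no conclusion of equivalence with rehabilitation will be drawn from p > 0.05.

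The cost is revised eligibility and analysis wording, possibly a few reference patients set aside, and a softer benchmark claim. No new assessments appear to be needed.

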### Group allocation

For the standard cardiac rehabilitation group, participants will be consecutively recruited prior to commencement of outpatient cardiac rehabilitation. Patients who are eligible for but not participating in cardiac rehabilitation will be randomly allocated to either their modular or conventional care group immediately following completion of the baseline assessment. Therefore, the researcher conducting each baseline assessment will be blinded to group allocation. Prior to study commencement, a computer-generated allocation sequence will be constructed using randomly permutated blocks [25]. An individual not involved in the study recruitment, data collection or analysis will produce consecutively numbered sealed opaque envelopes containing each participant's allocation. Following baseline assessment, the researcher will select the next consecutively numbered envelope and open it to reveal the allocated group. They will then notate the unique patient identifier on the front on the participants cover sheet. Therefore, group allocation will be concealed from the researcher conducting baseline assessments.

### Outcome measures

Assessments will be conducted in the hospital consulting rooms or in the participant's home, if they are unable to travel to the hospital. Demographic, subjective and objective information will be obtained during face-to-face assessments at baseline, three and 12 months. Information will include past history, nature of ACS, family history, age, medications and dose, presence of other cardiovascular disease and the nature and date of any revascularisation. In addition, contact details for each participant, their general practitioner and their cardiologist will be documented.

At three and 12 month follow-up, all baseline measures will be repeated during face-to-face assessments by a researcher blinded to group allocation. Additional collected information will include – details of unplanned hospital admissions, medications and doses along with details of any health interventions undertaken by the participant pertaining to their heart health, such as visits to the GP and attendance at community programs. For participants in the standard rehabilitation group, details of participation in the cardiac rehabilitation program will also be recorded such as duration and attendance at exercise and education sessions.

Modifiable risk factors to be measured are serum cholesterol, BP, smoking status, physical activity, overweight and depression. Lipids and substrates will be measured on a fasting blood sample within two weeks of assessment date. Participants will be referred to local pathology clinics by their primary care doctor and will visit the clinics by their own arrangement. Blood samples will be analysed for determination of total cholesterol (TC), low density lipoprotein cholesterol (LDL-C), high density lipoprotein cholesterol (HDL-C) and triglycerides (TG). Repeat blood tests will be carried out at the same pathology clinic wherever possible.

Resting BP will be measured from the brachial artery using an Omron digital automatic BP (Omron Healthcare Co Ltd Model M5, Japan). The automatic BP monitor will be calibrated against a mercury sphygmomanometer prior to study commencement and has been demonstrated to be accurate. The Omron M6 is accurate for BP to within 3 mmHg [26] and fulfills the recommendation criteria of the international protocol when tested against a mercury sphygmomanometer for diastolic and systolic BP readings [27]. For measurement, appropriate cuff size will be selected, each participant will be seated with the right arm supported and two consecutive blood pressure readings will be collected with one minute interval according to previously published guidelines [28].

Smoking status will be initially assessed by analysis of carbon monoxide (CO) levels using a hand-held breath analyzer or CO meter (Bedfont micro smokerlyzer, Scientific Ltd, England) using new mouthpieces (Airmet Scientific EC50MP500, Victoria Australia) for each participant, for infection control purposes. Participants will be expected to blow into the mouthpiece for the 15 seconds and the result are to be recorded in parts per million (ppm). The criteria for recent, within the past 24 hours, smoking will be an expired CO greater than 5 ppm [29]. Smoking status will be confirmed with self report to identify participants who concealed their true smoking status. Participants will be asked whether they had ever smoked, how long since they started or stopped and if they smoked, what is/was the average number of cigarettes smoked per day.

Physical activity levels will be assessed using the International Physical Activity Questionnaire (IPAQ) score [30]. The short, last-seven-days, self-administered format (last revised August 2002) comprises seven questions that seek information about the duration and frequency of vigorous and moderate physical activity as well as rest and walking in the past seven days. The IPAQ was developed as an international measure of physical activity, for use in adults, and has been tested for reliability and validity across 12 countries [31]. For final scoring, responses are divided into three categories, MET-minutes per week, average time spent sitting per day and a categorical level of physical activity. The categorical score is further divided into three levels – insufficiently active, sufficient activity and highly active.

For assessment of depressive mood, the Cardiac Depression Scale (CDS) score will be used [32]. The CDS was developed from the responses of cardiac outpatients and comprises 26 items with subscales relating to sleep, uncertainty, mood, cognition, hopelessness and inactivity. Some items are scored in reverse and raw scores are used for analysis where higher scores indicate depressed mood and a score of greater than 90 represents depressive mood. When assessed for test-retest reliability over two weeks scores were 64.9 ± 23.3 (mean ± SD) and 63.1 ± 23.0 with correlation coefficient of 0.86 and score difference of -1.9 ± 12.2 (mean ± SD). Permission has been obtained to administer the CDS from [name], Department of Cardiology (Austin & Repatriation Medical Centre, Australia).

For assessment of overweight, body mass index (BMI) will be calculated using the standard equation (BMI = weight kg/height m^2^). Each participant's body weight will be measured when lightly clothed and in bare feet using digital scales (Tanita EB727, Australia) to the nearest 0.1 kg. Height will be measured without shoes using a standiometer (Stature Meter 2 m 1013522, Livingston International Pty Ltd, NSW Australia) to the nearest 0.5 cm and according to best anthropometic practice [33].

Health related quality of life (HRQOL) will be assessed using the SF36 health survey [34], [35]. The SF36 comprises 11 items that ask for the participant's views about their health, how they feel and whether they are able to perform certain activities and has been tested for reliability and validity [34], [35]. A license has been obtained to use the SF36 for data collection from 300 patients on three occasions per participant (License number F1-052203-13860). SF36 scores will be coded, summed and transformed onto a scale from 0 (worst possible health) to 100 (best possible health) using the method described in the user manual [36].

Relative cardiac risk will be calculated using the LIPID score which was developed for use in secondary prevention [37]. An individual's risk score calculation involves aggregating risk point estimates corresponding to the patient's risk factor profile. Aggregate scores provide an indication of the level of risk for a future ACS. The scores are divided as low risk (≤ 4), medium risk (5–6), high risk (7–9) and very high risk (≥ 10) [37]. Further, each participants number of modifiable risk factors will be calculated using the cut points; TC > 4.0 mmol/L, SBP ≥ 140 mmHg, current smoking, physical inactivity using the categorical IPAQ score, BMI ≥ 30 kg/m^2^, known diabetes and a CDS score ≥ 90 for depression.

Each participant's knowledge of their own cardiovascular risk factors will also be assessed at baseline, three and 12 months. Participants will be asked if they can state any of their own modifiable risk factors for heart disease and the number stated will be compared to the each individual's actual number of modifiable risk factors. Participants will then be asked if they are able to state the Australian recommended targets for total cholesterol, BP, physical activity and whether or not smoking is recommended for people with CHD.

